**Trial Registration:**

National Institutes of Health Clinical Trials Registry (ClinicalTrials.gov identifier# NCT00776828).

## Background

Current guidelines recommend at least 6 months of dual anti-platelet agents, consisting of aspirin and a thienopyridine, after percutaneous coronary intervention (PCI) and ideally, 1 year of both drugs [1]. However, some patients experience acute thrombotic events, the incidence of which has been diverse from less than 1% to 3% [2,3] even with good adherence to this dual anti-platelet therapy (DAT), and also, late restenotic complication after PCI. In addition, as interventional cardiologists face more and more complex lesions, the risk of ischemic events, including cardiac events, may tend to rise. These problems raise the issue to whether there are effective additional methods or drugs to prevent ischemic complications.

Cilostazol is a selective phosphodiesterase-3 (PDE-3) inhibitor, which has various effects including vasodilatory, anti-platelet and partially, anti-inflammatory effect. Several investigators have focused on cilostazol as one of the candidate drugs that can reduce ischemic events after PCI. Inspite of the fact that cilostazol is metabolized by CYP 3A [4] and to a lesser degree 2C19 [5], the same pathway as that of clopidogrel, cilostazol was suggested to be effective in reducing platelet reactivity in vitro [6] and also, efficacious and safe in reducing thrombotic complications in the real world [7]. Also, several studies have suggested that cilostazol successfully and safely reduces restenosis rate after PCI [8-11]. In a meta-analysis, cilostazol has shown to be consistently helpful in reducing binary angiographic restenosis and repeat revascularization. But these data were derived mainly from the BMS era [12]. Data from a few randomized trials have suggested that cilostazol reduces late luminal loss also in drug-eluting stents (DES) [10,13]. But, these trials were underpowered to see whether cilostazol reduces the ultimate core endpoint of clinical trials, major adverse cardiac events (MACE) or major adverse cardiovascular/cerebrovascular events (MACCE). And the restricted inclusion criteria of the previous randomized trial cannot answer to the question whether cilostazol would be effective also in a routine clinical practice. These previous reports call for a large, randomized, controlled study to investigate whether cilostazol can really reduce MACE/MACCE after PCI in a real-world practice and also, for an extensive follow-up of these patients to see whether the effects persists in the long-term, as in a recent pooled analysis [14].

Additionally, there have been numerous questions as to whether there are significant interaction between clopidogrel and lipophilic statin and whether such interaction can be overcome by the addition of cilostazol. Although data on this matter is controversial but somewhat been in favor of being no significant in vivo interaction between clopidogrel and lipophilic statin [15], the interpretation and application of these data have been restricted by the unrandomized/unstratified manner of the studies [16-18] and non-prospective collection of the data [19]. Also, although the pleiotrophic effect of cilostazol in renal function has been demonstrated in some animal experiments [20,21], whether this holds true for humans have never been investigated.

In order to provide a definite answer to the above questions, we planned the 'Influence of **CIL**ostazol-based triple anti-platelet therapy **ON **Ischemic Complication after drug-eluting sten**T **implantation (**CILON-T**)' study. In this study, we compared the efficacy and safety of triple anti-platelet therapy (TAT), composed of aspirin, clopidogrel and cilostazol, with the conventional DAT by evaluating MACCE and platelet reactivity in an unselected population of patients receiving PCI with DES for coronary heart disease (CHD) in real-world practice. In addition, we would like to get answers for the issues whether lipophilic statin-clopidogrel interaction would influence the patient outcome and whether cilostazol can overcome such interaction, using atorvastatin (Lipitor^®^, Pfizer) dependent on cytochrome P450-3A4 (CYP3A4) for metabolism versus rosuvastatin (Crestor^®^, AstraZeneca) independent from CYP3A4.

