### Outcome measures

The primary endpoint of this study was the rate of MACCE, a composite ischemic vascular event following PCI, including cardiac death, nonfatal MI, TLR and ischemic stroke at 6 months in the DAT and TAT group. The key secondary endpoints defined a priori are

- P2Y12 reaction unit (PRU) as assessed by VerifyNow^® ^P2Y12 assay

- Cardiac death, nonfatal MI, TLR, target vessel revascularization (TVR), stent thrombosis and ischemic stroke

- MACCE according to the type of statin and its interaction with clopidogrel

- Bleeding, as defined according to the TIMI bleeding classifications [22], major bleeding defined by the presence of at least 1 of the following: intracranial bleeding (documented with magnetic resonance imaging, computed tomography, any other examination or autopsy), or clinically overt bleeding resulting in a 5 g/dL decrease in hemoglobin value (or, when hemoglobin values were not available, a 15% decrease in hematocrit).

- Angiographic outcome, such as late luminal loss, binary restenosis at 6 months' follow-up angiography

- Albumin-to-creatinine ratio

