#### Statistical Analyses

All analysis will be done by intention-to-treat method (all patients analyzed as part of their assigned treatment group). However, per protocol (patients analyzed as part of their assigned group only if they actually received their assigned treatment) and as-treated analysis will also be performed solely for descriptive comparison.

The primary endpoint of 6 months' MACCE will be analyzed using χ^2^-test on an intention-to-treat analysis. The hypothesis will be evaluated based on a superiority testing. The clinical secondary endpoints will also be tested based on χ^2^-test, similarly as primary endpoint testing. The endpoints will be analyzed in pre-specified subgroups, which includes the presence of diabetes mellitus, long lesions (lesion length≥28 mm), small vessel lesions (lesion diameter < 2.75 mm), age and sex. Also, most importantly, post-hoc analysis of MACCE according to the type of statin given (atorvastatin vs. rosuvastatin) will be done. Analysis of platelet function will be tested using repeated ANOVA method with the Bonferroni's correction.

Continuous variables will be presented as mean ± SD and compared with the use of unpaired Student's t-test or in the case of non-normal distribution, Mann-Whitney U test. Categorical variables will be summarized as number or percentages and compared with χ^2 ^or Fisher's exact test, as appropriate. Survival curves using all available follow-up data will also be constructed for time-to-event variables using Kaplan-Meier estimates and compared by log-rank test. A p-value < 0.05 will be considered statistically significant.

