### Issues sought in the CILON-T trial

In addition to the primary endpoint of whether TAT would be superior to DAT in reducing the ischemic vascular events after PCI, CILON-T trial is planned to assess several issues that remains to be answered. The issue of whether laboratory benefits are directly connected with clinical outcomes will be sought. Specifically, there have been papers demonstrating that PRU levels predicted adverse cardiovascular events in high risk patients [31-33] and that cilostazol reduced the average level of platelet activation in patients with coronary heart disease [6] and also, PRU level [34]. However, racial difference is one factor that can influence the platelet reactivity [35] and there remains a paradox between the higher level of PRU and lower rate of thrombotic events after DES implantation in Asians. Simply compared, the rate of stent thrombosis involving more than 3,000 patients around 1.5 years after DES implantation is 1.9% in Europeans [36] while 0.77% in Japanese [2]. In this CILON-T trial, we can get valuable information whether cilostazol-induced reduction of PRU levels would lead to beneficial clinical outcomes.

It is also expected to shed light on whether non-CYP3A4-metabolized statin is superior to CYP3A4-metabolized statin in terms of MAC(C)E and if so, whether cilostazol would be effective in reducing this difference. In vitro studies have persistently suggested that the effect of clopidogrel would be reduced by concomitant use of lipophilic statin [37,38] but large in vivo studies do not show trend toward detrimental effect of these types of statin [16-18,39]. However, these in vivo results come from observational registry data or post-hoc analysis of randomized clinical trials. Therefore, our data would add additional information to clopidogrel-statin interaction issue and also, if any, a new finding on the effect of cilostazol in this drug interaction.

In conclusion, we still do not know whether TAT is superior to DAT in reducing MACCE after DES implantation for coronary heart disease in the unselected real-world patients. Furthermore, whether cilostazol-induced PRU level reduction will turn out to improve clinical outcomes has never been elucidated. We hope to address these issues in the CILON-T trial where we enrolled a large unselected population of patients treated with DES for significant coronary heart disease.

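### The by-statin MACCE comparison has no stated split by DAT and TAT, and a smaller statin difference under TAT could not show that cilostazol overcomes the clopidogrel-statin interaction

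*Protocol article*

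**What the plan says.** The protocol article's Background poses two statin questions: "whether lipophilic statin-clopidogrel interaction would influence the patient outcome and whether cilostazol can overcome such interaction". Earlier in the same section it states that "cilostazol is metabolized by CYP 3A [4] and to a lesser degree 2C19 [5], the same pathway as that of clopidogrel". Atorvastatin is chosen as "dependent on cytochrome P450-3A4 (CYP3A4) for metabolism versus rosuvastatin", the latter being "independent from CYP3A4".

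Under Randomization and interventions, patients are randomized to DAT or TAT and also to one of the two statins. Clopidogrel is part of both antiplatelet regimens, and platelet reactivity is measured before discharge and at 6 months.

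The secondary endpoint in Outcome measures, repeated in Appendix 1, is "MACCE according to the type of statin and its interaction with clopidogrel". The only statin analysis in Statistical Analyses is that a "post-hoc analysis of MACCE according to the type of statin given (atorvastatin vs. rosuvastatin) will be done". It names neither a split by antiplatelet arm nor an arm-by-statin term. The method given there for platelet function is not tied to the statin question.

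In the Discussion, Issues sought in the CILON-T trial asks "whether non-CYP3A4-metabolized statin is superior to CYP3A4-metabolized statin in terms of MAC(C)E and if so, whether cilostazol would be effective in reducing this difference".

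**The concern.** Two separate things follow from this text.

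First, the comparison by statin type is labelled as the statin's interaction with clopidogrel, yet no arm is specified. Taken over all patients, it averages a DAT contrast without cilostazol and a TAT contrast with it. If cilostazol changes the statin difference, which is the possibility the trial wants to examine, the average matches neither arm.

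Second, the reason given for suspecting that atorvastatin affects clopidogrel is a shared CYP3A route. By the article's own account cilostazol uses that route too, so the same reasoning allows for an atorvastatin-cilostazol interaction. The article does not mention one. A statin difference that shrinks under TAT would then have at least two explanations that the four randomized groups cannot tell apart.

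At stake is what the trial may conclude on a stated secondary question: a real statin effect could be diluted, or a mechanism could be claimed that the design does not identify.

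**Working it through.** **The plan's own figure.** Inputs from Sample size calculation: MACCE 10% and 5%, two-sided 5%, power 80%, 1:1, 10% drop-out. With unpooled variance, n per arm = (1.96 + 0.84)² × (0.10×0.90 + 0.05×0.95) / 0.05² = 7.849 × 0.1375 / 0.0025 ≈ 432. Then 432 / 0.90 = 480 per arm, or 960 in total, which reproduces the plan. No sample size is given for the statin question. An equal statin split, which is assumed, gives 960 / 4 = 240 per cell, or 216 after 10% drop-out.

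**What the contrasts contain.** On an additive scale let

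- s = any direct difference between the statins,
- c = the clopidogrel-statin effect without cilostazol,
- r = the change in c when cilostazol is added (true overcoming),
- x = any cilostazol-atorvastatin effect.

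Then atorvastatin minus rosuvastatin is:

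- within DAT: d = s + c
- within TAT: d + k = s + c + r + x, so k = r + x
- all patients, equal arms: (d + d + k)/2 = d + k/2

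An effect of cilostazol on clopidogrel that is the same under both statins cancels within TAT and does not appear. The data give d and k. They do not give r and x separately, at any sample size.

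**Illustration on MACCE.** The effects are assumed. In every scenario the arm averages stay at the planning rates of 10% and 5%.

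| Scenario | DAT rosuva / atorva | TAT rosuva / atorva | DAT diff. | TAT diff. | All-patient |
|---|---|---|---|---|---|
| A: c = +4, cilostazol abolishes it (r = −4, x = 0) | 8% / 12% | 5% / 5% | 4 | 0 | 2 |
| B: c = +4 persists, offset by x = −4 (r = 0) | 8% / 12% | 5% / 5% | 4 | 0 | 2 |
| C: c = 0, x = +4 | 10% / 10% | 3% / 7% | 0 | 4 | 2 |
| D: c = 0, x = −4 | 10% / 10% | 7% / 3% | 0 | −4 | −2 |

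A and B have identical cell risks, so nothing in the 2×2 separates overcoming from offsetting. A and C give the same all-patient difference of 2 points, although C has no clopidogrel-statin effect. The within-DAT contrast does separate them (4 against 0).

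**Precision.** With equal cells and a common SD, the standard error is SD × √(2/240) = 0.0913 SD within DAT and SD × √(2/480) = 0.0645 SD over all patients. The ratio is √2 ≈ 1.41, whatever the SD. For PRU with an assumed SD of 80, these are 7.3 and 5.2 units. Multiplied by 2.80, the differences detectable with 80% power are about 20.5 and 14.5 units.

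**MACCE power, two-sided 5%, scenario A.**

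- Within DAT, 8% against 12%, 240 per cell: (0.04 − 1.96 × √(2×0.10×0.90/240)) / √((0.08×0.92 + 0.12×0.88)/240) = (0.04 − 0.0537)/0.0273 = −0.50, so power is about 31%. With 216 per cell it is about 28%.
- All patients, 6.5% against 8.5%, 480 per statin group: about 22%. Here the dilution outweighs the gain in precision.
- Arm-by-statin difference of 4 points: SE = √((0.0736 + 0.1056 + 0.0475 + 0.0475)/240) = 0.0338, so power is about 22% (20% with 216).
- Arm-by-statin difference detectable with 80% power, at 10% in both DAT cells and 5% in both TAT cells: 2.80 × √(2 × 0.1375/240) ≈ 9.5 points, or 10.0 with 216.

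**The case against.** The strongest reply is that the article nowhere says the arms will be pooled. The Discussion's follow-on question, "if so, whether cilostazol would be effective in reducing this difference", cannot be answered without looking at the statin difference by arm, so a split may be intended and may be set out in an analysis plan that is not shown. This stands in part: pooling is an inference from a by-statin comparison with no arm specified. What remains is that the one analysis written down carries the clopidogrel-interaction label without saying which arm or arms it refers to.

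A reader might also infer that the statin results are confounded. The documents do not support that. Both factors are randomized, so each contrast and the arm-by-statin term estimate what they say they estimate. Only the mechanism behind the term is open.

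Nor do the documents show that a cilostazol-atorvastatin interaction exists or how large it would be. It is a possibility raised by the article's own metabolic reasoning.

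It may also be said that overcoming is posed as a question and not laid down as a rule for reading results, and that whether the statin difference is smaller with cilostazol is an outcome-level question the 2×2 answers directly. That is correct. The limit applies to the step from that answer to the claim that cilostazol overcomes the clopidogrel-statin interaction.

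Finally, the d + k/2 averaging arises in any all-patient contrast when there is an interaction, and so says nothing specific about CYP3A. That is also true. It is a separate reason for reporting by arm.

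**Conclusion.** The point holds as a matter of specification and interpretation for a secondary question. An all-patient statin contrast would estimate d + k/2, which is half the DAT effect if cilostazol removes it completely. A smaller difference under TAT cannot be assigned to overcoming the clopidogrel-statin interaction rather than to a possible cilostazol-atorvastatin interaction.

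The second conclusion does not depend on sample size. It rests on the article's statements about CYP3A. The 4-point effects, the PRU SD of 80 and the equal cells of 240 are assumptions for illustration.

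Two further readings go too far. One is that the DAT arm isolates the clopidogrel-statin interaction: every patient receives clopidogrel, so the DAT contrast is free of cilostazol but still includes any direct difference between the statins. The other is that the main result is affected: the DAT against TAT comparison and its 960 patients are not.

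**What to change.** Report atorvastatin against rosuvastatin within DAT and within TAT, with confidence intervals and the arm-by-statin interaction term. Do this for PRU, which is already measured, and descriptively for MACCE. Any all-patient contrast can be kept alongside.

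Name the DAT contrast as the cilostazol-free estimate, and say that it still includes any direct statin difference. Describe the arm-by-statin term as the change in the statin difference when cilostazol is added, including any cilostazol-atorvastatin interaction, and do not present it as proof that cilostazol overcomes the clopidogrel-statin interaction.

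This changes analysis and wording only, with no new patients, measurements or treatment. The price is a DAT-only standard error about 1.4 times the all-patient one. MACCE power by arm and for the interaction is low, so those results should be given as estimates and not as tests expected to settle the question.

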## Methods/Design

### Study objectives, hypothesis and design

The primary objective of this study was to compare the efficacy of TAT with DAT in reducing 6 months' MACCE after PCI in those with documented CHD. The working hypothesis of this trial was 'TAT is superior to DAT in reducing 6 months' MACCE, the composite of cardiac death, nonfatal myocardial infarction (MI), ischemic stroke and target lesion revascularization (TLR) in CHD patients receiving PCI with DES'. The trial also addressed whether TAT is superior to DAT in reducing platelet reactivity and also, whether there is any clinical effect of statin-clopidogrel interaction on MACCE according to the type of statin. The protocol of the trial has been registered at http://www.clinicaltrials.gov (NCT00776828) and a brief flowchart of the whole study is summarized in Figure 1. The endpoints are summarized in Appendix 1.

**Figure 1 F1:**
[figure not shown]
Flowchart of the enrolled patients

### Patient population

Patients at least 18 years of age who had typical ischemic symptoms or positive stress test and a native coronary lesion (≥50% diameter stenosis by visual estimation on coronary angiogram and reference diameter≥2.5 mm)) were included in this study. Five high-volume centers in Korea participated and enrolled the patients in this multicenter, open-label, prospective, randomized trial. There were nearly no angiographic limitations about the number of lesions, vessels, location of lesions or their length, to investigate the effect of cilostazol in the real-world setting. The following patients were excluded from the study; cardiogenic shock; explicit side effect or contraindications to anti-platelet agents including cilostazol; concomitant treatment with any other anti-platelet agent or anticoagulant other than the study drugs; current user of cilostazol before the entry of study. The detailed inclusion and exclusion criteria are summarized in Appendix 2.

### Randomization and interventions

All patients received 300 mg aspirin and 300~600 mg clopidogrel loading before the procedure unless the patient had been taking these medications for at least 1 week before the procedure. Patients were randomized to receive either conventional DAT or TAT and also, randomly stratified to take equipotent doses of either atorvastatin 20 mg or rosuvastatin 10 mg per day before the interventional procedure. The patients were also stratified according to the enrolling medical centers/hospitals. A loading dose of cilostazol (Otsuka Korea) 200 mg was given immediately before the procedure. Random allocation of the patients was done via a Web-based computerized program separately managed at medical research collaboration center, Seoul National University Hospital. PCI was done according to the standard technique and the decision of the pre-dilatation and use of glycoprotein IIb/IIIa inhibitors were up to the operator's discretion. The target lesion/vessel was designated as the first lesion/vessel that was intervened. Platelet reactivity was measured by using the Ultegra Rapid Platelet Function Assay (VerifyNow^® ^Aspirin and VerifyNow^® ^P2Y12 assay, Accumetrics Inc., San Diego, California, USA) immediately before discharge.

After enrollment and index PCI procedure, clinical follow-up was planned at 1, 3, 6 months and all patients were recommended follow-up coronary angiography at 6 months according to local clinical practice. Platelet reactivity was also measured at 6 months after index procedure. The investigators were urged to follow the patients, either by office visits or by telephone contacts as necessary. Patient adherence to the study drug was checked at every outpatient visit and the decision of the drug discontinuation was always discussed and checked under the physician's recommendation.

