### Statistical Analysis

#### Sample size calculation

To test the hypothesis that TAT is superior to DAT in reducing MACCE at 6 months after PCI, based on the previous outcome data [10,13,23], we assumed that MACCE rate in DAT and TAT group would be 10% and 5% respectively. Using a superiority design, an estimated total of 960 patients was needed to ensure a power of at least 80% to detect a 5% difference in the composite of ischemic vascular events between the two anti-platelet therapy groups using a two-sided t-test, with a sampling ratio of DAT:TAT at 1:1, bilateral risk set at 5% and drop-out rate estimated to be 10%.

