## Appendix

### Appendix 1. Endpoints of CILON-T trial

#### Primary endpoints

MACCE (composite of cardiac death, nonfatal MI, TLR and ischemic stroke)

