#### Angiographic inclusion criteria

Target lesion(s) located in a native coronary artery with visually estimated diameter≥2.5 mm

Target lesion(s) amenable to PCI (left main, bifurcation and chronic total occlusion lesion included)

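### The target lesion is only the first lesion treated, so repeat revascularization confined to another index-stented lesion does not count towards primary MACCE

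*Protocol article*

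**What the plan says.** All places are in the protocol article.

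- **Target lesion rule** (Randomization and interventions): "The target lesion/vessel was designated as the first lesion/vessel that was intervened". The rule is singular and covers the vessel as well as the lesion.
- **Primary endpoint** (Outcome measures): MACCE, "including cardiac death, nonfatal MI, TLR and ischemic stroke at 6 months in the DAT and TAT group". Appendix 1 lists the same components: "MACCE (composite of cardiac death, nonfatal MI, TLR and ischemic stroke". TLR is the only revascularization among them.
- **Secondary endpoints** (Outcome measures): "Cardiac death, nonfatal MI, TLR, target vessel revascularization (TVR), stent thrombosis and ischemic stroke". TVR appears here and not in the primary composite.
- **Who is enrolled** (Patient population): "There were nearly no angiographic limitations about the number of lesions, vessels, location of lesions or their length".
- **Eligibility wording** (Appendix 2, Angiographic inclusion criteria): "Target lesion(s) located in a native coronary artery with visually estimated diameter≥2.5 mm" and "Target lesion(s) amenable to PCI (left main, bifurcation and chronic total occlusion lesion included". Both use the plural.
- **Planning rates** (Sample size calculation): "we assumed that MACCE rate in DAT and TAT group would be 10% and 5% respectively".

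**The concern.** The trial asks whether adding cilostazol reduces ischemic events after DES implantation in unselected patients. The Discussion expects the drug to limit neointimal growth and restenosis. A systemic drug should do that at every stented lesion, not only at the one treated first.

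Under the written rule, a patient with two stented lesions whose second stent restenoses and is treated again has no TLR. If the second lesion is in another vessel, there is no TVR either. Follow-up angiography at 6 months is recommended for all patients, so such restenosis could be found and treated without an MI. That patient would be counted as free of MACCE.

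Two things are at stake: whether the primary endpoint captures the stent failures the trial wants to prevent, and whether enough events are counted to keep the planned power. The plural in Appendix 2 adds a practical problem, because two adjudicators could classify the same revascularization differently.

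**Working it through.** **Step 1: what counts as a primary event.**

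| Repeat revascularization within 6 months, no MI, cardiac death or stroke | TLR | TVR | MACCE |
|---|---|---|---|
| First lesion treated | yes | yes | yes |
| Another index-stented lesion, same vessel | no | yes | no |
| Another index-stented lesion, other vessel | no | no | no |

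Nothing else in the article returns the last two rows to the primary endpoint. The Appendix 2 wording is an eligibility criterion and does not redefine TLR. The adjudication committee's detailed criteria are not shown; they are described as resting on the protocol.

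**Step 2: reproduce the plan's sample size.** Inputs from Sample size calculation: p1 = 0.10, p2 = 0.05, two-sided 5%, power 80%, 1:1 allocation, 10% drop-out. With unpooled variance:

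n = (1.960 + 0.842)² × (0.10×0.90 + 0.05×0.95) / 0.05² = 7.849 × 0.1375 / 0.0025 = 431.7, so 432 per arm.

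432 / 0.9 = 480 per arm, total 960. The plan's figure reproduces exactly.

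**Step 3: planned power.** With the pooled two-proportion formula:

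power = Φ{ [(p1 − p2)√n − 1.960 √(2p̄(1 − p̄))] / √(p1(1 − p1) + p2(1 − p2)) }, where p̄ = (p1 + p2)/2.

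- n = 432 (after drop-out): (1.0392 − 0.7301) / 0.3708 = 0.834, power 79.8%.
- n = 480 (all randomized): (1.0954 − 0.7301) / 0.3708 = 0.985, power 83.8%.

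**Step 4: sensitivity.** Let f be the share of patient-level MACCE that occurs only as revascularization of a non-first lesion. The document does not give f, so the values below are assumptions. They also assume that the 10% and 5% rates counted TLR at every treated lesion. The relative risk is held at 0.5, so the counted rates become 0.10(1 − f) and 0.05(1 − f). For example, f = 20% gives 8% and 4%; with n = 432, (0.8314 − 0.6583) / 0.3347 = 0.517, power 69.8%.

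| f (assumed) | Counted rates | Power, 432 per arm | Power, 480 per arm | Total N for 80% (pooled, 10% drop-out) |
|---|---|---|---|---|
| 0% | 10.0% / 5.0% | 79.8% | 83.8% | 968 |
| 5% | 9.5% / 4.75% | 77.5% | 81.7% | 1024 |
| 10% | 9.0% / 4.5% | 75.1% | 79.4% | 1084 |
| 15% | 8.5% / 4.25% | 72.5% | 77.0% | 1152 |
| 20% | 8.0% / 4.0% | 69.8% | 74.3% | 1230 |

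The pooled formula gives 968 rather than 960 at f = 0 because of the variance convention alone.

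**The case against.** **The power loss may be nil.** If the studies behind the 10% and 5% rates counted TLR at one lesion per patient, the plan already allows for the rule and nothing is lost against it. The article does not say how those rates were built. This objection stands, so the range must include zero.

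**The loss is easy to overstate.** A reader might assume 1.2 to 1.6 lesions per patient with equal risk, infer that (L − 1)/L = 17% to 38% of TLRs fall on later lesions, and multiply by an assumed TLR share of MACCE of 50% to 70% to lose 8% to 26% of primary events. That treats lesion events as patient events. A patient who also has a first-lesion TLR, MI, ischemic stroke or cardiac death is still counted, and every input is assumed. The calculation overstates the loss even on its own assumptions.

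**Bias between arms.** A reader might infer that the rule invites bias, since the order of treatment is settled after randomization by an operator in an open-label trial. The article gives no mechanism by which knowing the arm would change which lesion is treated first, and the rule is mechanical. Bias is not shown, and leaving out events in this way does not by itself produce it.

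**Failures elsewhere are not all lost.** Failure at another lesion still counts if it presents as MI or cardiac death, and stent thrombosis is a secondary endpoint in its own right. Only revascularization without another component event drops out.

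**The article does not define TLR in so many words.** This is true, and the unseen adjudication criteria may be more detailed. But they were to follow the protocol, and the only designation of the target lesion shown is the single-lesion one.

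**Conclusion.** The concern holds as a defect in the definition of the primary endpoint. The stated rule confines TLR to one lesion per patient in a trial that admits multi-lesion and multivessel disease almost freely, and it does not match the plural used in Appendix 2. What is lost is completeness of the endpoint and some counted events.

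The size cannot be derived from the document. It runs from no loss of power to a fall of about 10 percentage points if 20% of MACCE were uncounted (79.8% to 69.8% with 432 per arm; 83.8% to 74.3% with 480). With 480 per arm, power stays above 80% at a 5% loss and slips just below it at 10%. These figures rest on a constant relative risk and on planning rates that counted all treated lesions.

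**What to change.** - Define target lesions as all lesions treated with a DES at the index procedure, and target vessels as all vessels containing them.
- Count TLR once per patient, as the first revascularization of any target lesion.
- Keep the first-lesion rule, if wanted, only to choose one lesion per patient for late luminal loss.
- Make Randomization and interventions agree with Appendix 2.
- State which definition of TLR the 10% and 5% rates assume.

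Timing matters. The article reports 960 patients as already randomized in an open-label trial, so the change must be made and dated before any comparison of outcomes by arm. If that is no longer possible, keep the first-lesion definition as primary and report MACCE with all treated lesions as a prespecified sensitivity analysis.

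The cost is a change of wording, reclassification of recorded revascularizations by lesion, and a late change to an endpoint definition that must be disclosed. The case report form is not shown, so whether it records the lesion for each revascularization needs to be confirmed.
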